## Abstract

**Background:**

Many women with HIV (WWH) have suboptimal adherence to oral antiretroviral therapy (ART) due to multilevel barriers to HIV care access and retention. A long-acting injectable (LAI) version of ART was approved by the US Food and Drug Administration in January 2021 and has the potential to overcome many of these barriers by eliminating the need for daily pill taking. However, it may not be optimal for all WWH. It is critical to develop tools that facilitate patient-provider shared decision making about oral versus LAI ART modalities to promote women’s adherence and long-term HIV outcomes.

**Objective:**

This study will develop and pilot test a web-based patient decision aid called i.ART+support (i.ARTs). This decision aid aims to support shared decision making between WWH and their providers, and help women choose between oral and LAI HIV treatment.

**Methods:**

The study will occur in 3 phases. In phase 1, we will utilize a mixed methods approach to collect data from WWH and medical and social service providers to inform *i.ARTs* content. During phase 2, we will conduct focus groups with WWH and providers to refine *i.ARTs* content and develop the web-based decision aid. In phase 3, *i.ARTs* will be tested in a randomized controlled trial with 180 women in Miami, Florida, and assessed for feasibility, usability, and acceptability, as well as to evaluate the associations between receiving i.ARTs and viral suppression, ART pharmacy refills, and clinic attendance.

**Results:**

This study was funded in March 2021. Columbia University’s IRB approved the study protocols (approval number IRB-AAAT5314). Protocols for phase 1 interviews have been developed and interviews with service providers started in September 2021. We will apply for Clinicaltrials.gov registration prior to phase 3, which is when our first participant will be enrolled in the randomized controlled trial. This is anticipated to occur in April 2023.

**Conclusions:**

This study is the first to develop a web-based patient decision aid to support WWH choices between oral and LAI ART. Its strengths include the incorporation of both patient and provider perspectives, a mixed methods design, and implementation in a real-world clinical setting.

**International Registered Report Identifier (IRRID):**

DERR1-10.2196/35646

## Introduction

Suboptimal antiretroviral therapy (ART) adherence among people with HIV has constrained efforts to curb the HIV epidemic in the United States [1]. Women face myriad barriers to HIV care and treatment and have historically been underrepresented in clinical trials for HIV treatment [2,3]. As a result, women with HIV (WWH) have lower care retention (58% retention versus 65% retention in the overall US population), which contributes to their increased mortality compared with men [1,4-7]. There is therefore an urgent need for strategies that optimize care engagement and viral suppression among WWH.

Long-acting injectable (LAI) ART may be a strategy to improve ART adherence and HIV outcomes for women [2,3,8]. The first LAI ART (cabotegravir/rilpivirine), which consists of monthly intramuscular injections rather than daily pills, was approved by the US Food and Drug Administration (FDA) in January 2021; a bimonthly version was approved in February 2022; and other LAI ART drugs are in advanced stages of clinical trials and expected to be available for HIV treatment in the near future [9]. Women comprised only 8%-33% of phase 2 and phase 3 LAI ART trial participants, and pregnant women were not included [10-13]. As such, gender-specific barriers, pregnancy-related interactions [13] and characteristics that promote ART adherence among WWH remain underexplored [14-16]. Furthermore, LAI ART research has occurred largely among clinical trial participants, whose optimal medication adherence and clinic attendance do not represent the majority of WWH [17].

While preliminary research suggests that most WWH would prefer LAI ART over their current daily oral medication [18], this research has also identified multilevel barriers to LAI ART uptake. At the *individual level*, these include women’s concerns about side effects, pregnancy-related interactions, and drug resistance if LAI ART is discontinued without oral ART initiation; at the *clinic level*, barriers include medical mistrust due to historic sterilization campaigns [19] and lack of provider knowledge and willingness to offer LAI ART; and at the *structural level*, barriers include gender-specific socioeconomic inequalities and dynamics such as low-wage employment with unstable scheduling, lack of transportation, and care-taking responsibilities. Furthermore, FDA indication still requires viral suppression via oral ART prior to initiating LAI. These multilevel barriers could all complicate the frequent visits that LAI ART administration will require [18,20-23]. WWH and providers may benefit from tools and strategies that help them to identify and address barriers that prevent uptake of, and adherence to, LAI ART.

Shared decision making in medical settings is often accomplished using patient decision aids. These evidence-based tools promote equity in medicine by increasing patients’ knowledge, decision-making power [24,25], and health outcomes [26-28]. This approach can also lower medical paternalism [24,29-31]. Patient decision aids can improve medication adherence directly [32], as well as through mediating factors (eg, patient satisfaction [33-35], efficacy [36-38], and communication) [33,39,40]. These tools are ideal for preference-sensitive decisions with multiple options [41,42]; however, no patient decision aids yet exist to facilitate women’s choice between HIV treatment modalities. New tools are urgently needed to ensure the successful and equitable integration of new technologies such as LAI ART into clinical settings [43].

This paper describes the protocol for a mixed methods study to develop, refine, and test a patient decision aid for WWH, called i.ART+support (*i.ARTs*). *i.ARTs* will facilitate shared decision making between WWH and providers to determine which HIV treatment (oral or LAI ART) best fits a woman’s preferences, addresses her unique barriers, and, in doing so, facilitates adherence. This study will be conducted within the MACS/WIHS Combined Cohort Study (MWCCS) [44] and will fill the aforementioned gaps in existing research regarding patient decision aids for WWH. MWCCS is the largest and oldest prospective epidemiological cohort study of HIV in the United States. The current cohort includes approximately 1800 women from geographically diverse sites across the United States. Each of these has associated clinical sites with medical and social service providers who work with WWH. The aim of this paper is to provide an overview of all procedures for our study focused on developing a patient decision aid to support WWH as they choose between LAI and oral formulations of ART.

## Methods

### Overview of the Study

Study methods are aligned with current systematic approaches to patient decision aid development [36,45,46], and will occur in 3 phases (Figure 1). Each phase is associated with 1 of the following study aims. *Phase 1* will generate data to inform *i.ARTs* content using mixed methods research with WWH and providers. *Phase 2* will iteratively develop *i.ARTs* as a web-based patient decision aid. *Phase 3* will pilot test *i.ARTs* to assess feasibility, acceptability, and usability and to compare decisional outcomes and adherence data (including viral suppression, ART refills, and clinic attendance) between *i.ARTs* recipients and standard of care (control) WWH (n=180; 90 per group). Each phase includes distinct data collection activities, which are summarized in Table 1.

**Figure 1 figure1:**
[figure not shown]
Study overview. *i.ARTs*: i.ART+support; LAI ART: long-acting injectable ART; MWCCS: MACS/WIHS Combined Cohort Study; WWH: women with HIV.

**Table 1 table1:** Overview of data sources and participants.

Phase	Data source	Participants	Scope of data	Purpose
1	MWCCS^a^ 2020 cohort survey	1500 WWH^b^ at 9 MWCCS sites	WWH perspectives on LAI ART^c^ and decision making; identify relevant barriers and facilitators to LAI ART uptake; characteristics of women who are most likely to adhere to LAI ART	Generate *i.ARTs*^d^ content
1	Provider interviews	45 medical/social service providers at MWCCS sites	Provider perspective on characteristics of women most likely to adhere to LAI ART; reasons providers would not offer LAI ART to a woman for whom it is clinically indicated; provider perceptions of multilevel barriers and facilitators to WWH’s ART use	Generate *i.ARTs* content
2	Focus groups	MWCCS providers, WWH in Miami, Florida	Feedback on successive iterations of *i.ARTs*	Develop and refine *i.ARTs* content
3	Baseline and postvisit survey	180 WWH (90 from the intervention/*i.ARTs* arm and 90 from the control arm)	Information on decisional conflict (baseline and post), acceptability and satisfaction (post only), and sociodemographic and behavioral moderators (baseline only)	Assess *i.ARTs* acceptability and usability outcomes, assess impact of moderators
3	Exit interviews	20 WWH who receive *i.ARTs* and 10 providers	WWH and provider perspectives on *i.ARTs* tool	Assess *i.ARTs* feasibility, usability, acceptability
3	Electronic medical record data	180 WWH	*i.ARTs* adherence data for study participants, including clinic visits, medication refills, and viral load data	Preliminary impact of *i.ARTs* data on treatment-related outcomes

^a^MWCCS: MACS/WIHS Combined Cohort Study.

^b^WWH: women with HIV.

^c^LAI ART: long-acting injectable antiretroviral therapy.

^d^*i.ARTs*: i.ART+support

### Phase 1: Formative Work to Inform *i.ARTs* Content

To ensure *i.ARTs* addresses a comprehensive array of factors that influence LAI ART uptake, phase 1 includes data collection that incorporates the perspectives of both WWH and providers at MWCCS sites.

*Phase 1a* will quantitatively assess WWH perspectives on LAI ART and decision making, identify relevant barriers and facilitators to LAI ART uptake, and identify the characteristics of women who are most likely to adhere to LAI ART. It utilizes survey data administered to the MWCCS study cohort starting in October 2020. Historically, this sample included 1661 WWH of whom 1610 have a history of taking oral ART [44]. None have participated in LAI ART clinical trials. Full descriptions of participant recruitment, selection, enrollment, and study procedures for MWCCS are available elsewhere [44]. Survey responses from the 2020 cohort were collected from fall 2020 through summer 2021, and include 15 items that assess LAI ART–related knowledge, interest, and potential barriers and facilitators to use. We will use multivariable logistic regression models to identify factors associated with WWH’s interest in, and barriers and facilitators to, LAI ART. While potential barriers and facilitators to LAI ART uptake can change over time (eg, transportation/housing), we will be looking at these associations cross sectionally and thus capturing these barriers at a given moment in time. The sample size provides the power to detect modest effect sizes in a multivariable logistic regression analysis (odds ratios ranging from 1.4 to 1.6), even with a low probability of LAI interest and a high squared multiple correlation (0.4-0.5) between predictor variables. This sample size will allow for subgroup analyses and still detect moderate effect sizes (eg, by age or MWCCS site).

*Phase 1b* assesses HIV provider perspectives on LAI ART for their female clients. It involves in-depth interviews with 30 medical (eg, infectious disease physicians, advanced practice registered nurses) and 15 social service providers (eg, case managers, HIV clinical social workers) who serve WWH across 9 MWCCS sites and affiliated clinical sites.

Provider participants will complete a 1-time, 45-60-minute interview, and receive a US $75 gift card as compensation. Interview domains will include (1) providers’ perceived characteristics of women most likely to adhere to LAI ART, particularly compared with oral ART (eg, housing, oral ART adherence, caregiving responsibilities, and clinic attendance); (2) reasons providers would not offer LAI ART to a woman for whom it is clinically indicated; (3) providers’ perspectives on decision making in the clinical setting and their experience in deciding which ART medications their WWH clients should take; and (4) multilevel barriers and facilitators to WWH’s ART use and solutions to overcome these adherence barriers. These domains are determined by formative work by the study team [18,20,22,23]. Interviews will be digitally recorded and professionally transcribed. Transcripts will be coded using a set of codes inductively identified from the data; these will be supplemented by codes derived from the existing literature. A thematic content analysis approach will be used to identify key findings within domains of interest [47]. Data will be summarized and applied to activities in phase 2, described in the following section.

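### Phase 1a survey spans the January 2021 LAI ART approval but is analysed as one point in time; survey date belongs in the models

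*Protocol article*

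**What the plan says.** All of this is in the protocol article. The Phase 1 section dates the survey twice: "It utilizes survey data administered to the MWCCS study cohort starting in October 2020" and "Survey responses from the 2020 cohort were collected from fall 2020 through summer 2021". Its 15 items cover LAI ART-related "knowledge, interest, and potential barriers and facilitators to use". The Introduction says that the first LAI ART "was approved by the US Food and Drug Administration (FDA) in January 2021".

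The analysis is stated as: "We will use multivariable logistic regression models to identify factors associated with WWH’s interest in, and barriers and facilitators to, LAI ART". On time, the section says: "While potential barriers and facilitators to LAI ART uptake can change over time (eg, transportation/housing"), and continues that "we will be looking at these associations cross sectionally and thus capturing these barriers at a given moment in time". On subgroups: "This sample size will allow for subgroup analyses and still detect moderate effect sizes (eg, by age or MWCCS site").

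Table 1 gives 1500 women at nine sites and names the purpose of the survey as generating i.ARTs content. The Expected Challenges section discusses changing FDA approvals for the Phase 3 pilot. There it accepts that the newly approved bimonthly formulation may influence women's preferences while the study runs. Nothing comparable is said about Phase 1a.

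**The concern.** Women surveyed in the first months rated a product that was not yet approved, and those surveyed later rated an approved one. Knowledge and interest are the kind of answer that an approval could plausibly shift, and the article accepts that mechanism for Phase 3. The change over time that it acknowledges in Phase 1a concerns barriers and facilitators, with transportation and housing as examples. It does not mention the changed status of the product being rated.

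The problem arises when calendar time is related to a predictor. Nine sites need not have surveyed at the same pace, and women seen early or late in a wave may differ in the characteristics being modelled. A site or characteristic that only marks a later survey date would then show an association with interest or barriers. For site, it is the comparison between sites that is exposed. An association within one site is affected only if the predictor tracks survey date there. At stake is how well the formative evidence describes which women are interested and what stands in their way.

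**Working it through.** **1. Does the window straddle the approval?** Yes: it starts in October 2020, the approval is in January 2021, and it ends in summer 2021. Assume even response from 1 October 2020, and take 21 January as the approval day (the article gives only the month). Then 112 days precede approval. The pre-approval share is 112/273 = 0.41 if the survey ended on 1 July, 112/334 = 0.34 on 31 August, and 112/355 = 0.32 on 21 September 2021. Letting the day run over all of January widens this to 92/355 = 0.26 through 122/273 = 0.45. On these assumptions both eras are well represented, so an era term can be estimated.

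**2. The plan's own figure.** The article states detectable odds ratios (OR) of 1.4 to 1.6, with a low probability of LAI interest and a squared multiple correlation R² of 0.4 to 0.5. Assume two-sided α = 0.05 and 80% power, which that section does not state. The formula is β² = (1.96 + 0.84)² / [N·P(1−P)·(1−R²)], with OR = exp(β) per SD of a continuous predictor. With N = 1500:

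- P = 0.10: OR 1.37 (R² = 0.4) to 1.41 (R² = 0.5)
- P = 0.05: OR 1.53 to 1.60

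The stated range is reproduced for P of about 5–10% and is not in dispute. A balanced binary predictor would need OR 1.86 to 1.98 at P = 0.10.

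**3. How large could the artefact be?** Suppose the predictor has no true effect. Let p0 and p1 be the interest before and after approval, linked by a period OR, and let s be a group's share surveyed before approval. Group interest is s·p0 + (1−s)·p1. The spurious OR is the ratio of the two groups' odds. The values of p0, the period OR and s are all assumed, since the article gives none of them.

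Worked case: p0 = 0.20 and period OR 2 give p1 = 0.50/1.50 = 0.333.

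- Shares 40% and 20%: interest 0.280 and 0.307, OR 1.14
- Shares 50% and 10%: interest 0.267 and 0.320, OR 1.29

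Full grid at p0 = 0.20:

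| Period OR | 40% vs 20% | 50% vs 10% | 60% vs 10% |
|---|---|---|---|
| 1.5 | 1.08 | 1.17 | 1.22 |
| 2 | 1.14 | 1.29 | 1.39 |
| 3 | 1.22 | 1.49 | 1.66 |

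Over p0 from 0.10 to 0.50 and period OR from 2 to 3, the 40/20 split gives 1.13 to 1.26 and the 50/10 split gives 1.28 to 1.58. Equal shares (30% and 30%) give exactly 1.00.

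**4. Would it be noticed as a finding?** Take two groups of 750, unadjusted, with p0 = 0.20 and period OR 2. The chance of a significant difference with no true effect is 0.20 for the 40/20 split, 0.62 for 50/10 and 0.82 for 60/10, against a nominal 0.05.

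**The case against.** The strongest reply is that the article lists no covariates, so the absence of a survey-date term shows little: a condensed article may leave the adjustment set to a fuller plan. That stands. One cannot infer that survey date has been ruled out. The point rests on the stated single-moment, cross-sectional treatment of a window that contains the approval.

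A second reply is that the sentence only means that each woman's changeable circumstances are measured once, and that the collection window is stated openly just before it. That is a fair reading, and the window needs no correction. But measuring each woman once does not remove the calendar difference between women.

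Three stronger readings are tempting and not supported:

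- **That the Phase 1a associations are biased.** The article gives no survey dates by site and no interest by era, so only the possibility is shown.
- **That the artefact falls in the range the survey is powered to detect.** Some numbers overlap, but the stated 1.4 to 1.6 assumes low interest and is reproduced per SD of a continuous predictor. The illustrations above are contrasts between two groups, so the two are not on the same footing.
- **That a spurious marker would pass straight into the tool.** Content also draws on provider interviews, which began in September 2021, after approval, and it is shaped by two sets of five focus groups. The suggested modality comes from each woman's own rankings and health history. No population odds ratio or site term is described as an input.

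**Conclusion.** The point holds as a conditional one. The survey straddles the approval, and the stated single cross-section does not separate era from site or patient characteristics. Under an assumed approval effect of OR 2 to 3, the artefact is about 1.1 to 1.25 for a mild imbalance in survey date and about 1.3 to 1.6 for a strong one. It is smaller for a weaker approval effect, larger for more extreme imbalance, and nil under balance. None of these inputs is in the article, so the actual size is unknown.

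This is a minor improvement to a formative survey. A reader might extend it to the trial itself, but the randomized Phase 3 comparison, its outcomes and its sample size do not depend on it.

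**What to change.** 1. Include survey date in the Phase 1a logistic models and in the comparisons between sites, at minimum as a before/after-approval indicator.
2. Report the distribution of survey dates by site.
3. Check whether interest, knowledge and the main barriers differ by era. Where they do, report era-specific estimates as a sensitivity analysis.

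The main estimates should keep all responses. Restricting them to women surveyed after approval would discard roughly a third of the data under even response (32–41% in step 1), a trade-off that this concern does not justify.

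The cost is one covariate among about 1500 women and no new data, assuming that the survey date was recorded. Precision will fall for sites surveyed mostly in one era, because there the indicator and the site can be separated only weakly. The date table by site will show where this applies.

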### Phase 2: *i.ARTs* Development

Phase 2 utilizes sequential focus groups with both WWH and medical and social service providers to determine the content of *i*.*ARTs* and create and revise the *i.ARTs* web-based app. Existing research indicates that web-based decision aid tools have advantages over paper-based ones, including interactive interfaces and visual filtering and sorting options [48]. This stage of *i.ARTs* development will follow International Patient Decision Aids Standards Collaboration (IPDAS) guidelines [46,49,50] and use the Ottawa Decision Support Framework [27,51-53]. This framework explains the relationship between participants’ decisional needs and decisional quality using both prescriptive [54] (based on rational actions, highest expected utility) and descriptive [55] (preferences-based, nonrational) decision theories.

An overview of the planned *i.ARTs* development process is included in Figure 2. We will conduct 2 sets of 5 focus groups: 1 set with 10 MWCCS providers recruited from the Phase 1 interview participants and the other set with 8-10 WWH recruited from the Miami MWCCS–affiliated clinical site. The Miami MWCCS site was selected due to the city’s high HIV incidence and low ART adherence, as well as a racially/ethnically diverse population [56-58]. WWH will be selected from Miami’s MWCCS community advisory board as well as by local MWCCS collaborators to ensure inclusion of women with a diverse range of perspectives, clinic attendance, and adherence. Each focus group will meet for approximately 60 minutes, and participants will be compensated US $40 per session for their time. We will record and transcribe the focus groups and review them to identify which items and topics should be included in the patient decision aid, as well as how to word specific items.

Focus groups will use data from phase 1 to develop and finalize *i.ARTs* content and iteratively refine the web-based version of *i.ARTs* to prepare for the phase 3 pilot testing according to the schedule in Figure 3. Between each set of focus group meetings, the study team will integrate feedback from both the provider and WWH groups and either create the suggested content or make the suggested improvements to the *i.ARTs* program. This will ensure that women’s perspectives and realities will be captured to tailor the content within the patient decision aid.

**Figure 2 figure2:**
[figure not shown]
*i.ARTs* decision aid development process and focus groups (FGs). *i.ARTs*: i.ART+support.

